### Statistical considerations and sample size estimation

Patients are included for primary analysis if information about complications is available up to the day of discharge. Non-compliant and compliant patients will be compared with respect to age and sex distribution.

About 80 patients from the INSECT-Trial will serve as control group. Using the 1:4 rule, up to 320 patients could be collected in a sensible manner. Within a reasonable time-frame of 1 year, 150 patients could be enrolled into the ISSAAC-Trial. Assuming a drop-out rate of 7%, 140 patients could be subjected to an analysis with respect to the primary endpoints. This would be sufficient to construct a 90% confidence interval around the estimate that would not cover the value of 25% with a power of 10% when the true event rate is at 15%.

It is expected that the historical control group will comprise about 130 patients who had been enrolled into the INSECT-Trial. To make the comparison with the historical control group as meaningful as possible (using an "information per patient" metric), the size of the MonoMax^® ^group should not exceed the size of the control group by too much und has been accordingly established at 150 patients, allowing for 10 drop-outs.

Each participating centre should add at least 1/4 to the patients it had recruited during the INSECT-Trial, e.g. Marburg at least 7 patients and the other three at least 10 patients each. In order to avoid a centre effect, no participating hospital should include more than 80 patients.

The level of significance for the confidence intervals is set at 95 and 90% in order to perform a one-sided test of significance against the 25% event rate stated in the null hypothesis.

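### The sample-size statement gives the type II error (10%) as the power, which is about 90%, and the two confidence levels named for the one-sided test need their sidedness and the deciding level stated

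*Protocol article*

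**What the plan says.** Everything is in the protocol article, section Statistical considerations and sample size estimation. The section states that "150 patients could be enrolled into the ISSAAC-Trial" and, "Assuming a drop-out rate of 7" percent, that "140 patients could be subjected to an analysis with respect to the primary endpoints". It then says this number is enough to "construct a 90% confidence interval around the estimate that would not cover the value of 25% with a power of 10" percent, "when the true event rate is at 15" percent. This is the only power figure in the article.

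The last sentence of the section returns to the test: "The level of significance for the confidence intervals is set at 95 and 90% in order to perform a one-sided test of significance", the comparison being with the 25% event rate of the null hypothesis. It does not say whether each level belongs to a one-sided bound or a two-sided interval, or which of the two decides the primary test.

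**The concern.** There are two separate matters.

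First, a power of 10% cannot support a claim that the sample is sufficient. Read literally, the trial would miss its target nine times in ten under its own planning assumption. All the inputs are given, so the figure can be checked directly.

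Second, 95 and 90% are confidence levels, not significance levels, and two of them are attached to one test. Depending on sidedness they describe either one criterion or two. If they are two, a small band of event counts passes under one and fails under the other, and the power statement is true for only one of them. At stake are the pass mark of the primary test and the power that goes with it.

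**Working it through.** **Inputs** (all from the section named above): 150 enrolled; 7% drop-out; 140 analysable; null rate p0 = 0.25; assumed true rate p1 = 0.15; 90% confidence interval; stated power 10%.

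**Step 1: analysable number.** 150 × 0.93 = 139.5, about 140. This agrees with the article.

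**Step 2: try to reproduce the 10%.** The upper limit of a two-sided 90% interval corresponds to a one-sided 5% test. The normal (score) formula is

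power = Φ{[(p0 − p1) − z₀.₉₅·√(p0·q0/n)] / √(p1·q1/n)}

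- √(0.1875/140) = 0.0366, times 1.645 = 0.0602
- √(0.1275/140) = 0.0302
- (0.10 − 0.0602)/0.0302 = 1.32, so power = 90.6%

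The 10% is not reproduced. Its complement is.

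**Step 3: exact binomial.** Find the largest event count whose upper limit is below 25%, then the chance of that count or fewer. With a two-sided 90% Clopper-Pearson interval, 26/140 has an upper limit of 24.8% and 27/140 one of 25.6%, so the limit is 26. Wilson gives the same count.

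- P(X ≤ 26 | 0.15) = 0.901, so power is 90.1% and type II error 9.9%
- P(X ≤ 26 | 0.25) = 0.045, so one-sided error is 4.5%

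**Step 4: could another method give 10%?** Across Wald (with and without continuity correction), Wilson, Agresti-Coull and Clopper-Pearson limits and several normal approximations at n = 140, power runs from 86% to 95% for a 90% interval, 78% to 91% for a 95% interval, and 93% to 98% for an 80% interval (that is, if 90% meant a one-sided bound). None comes near 10%.

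**Step 5: work backwards.** n = [(z_α·√(p0·q0) + z_β·√(p1·q1))/(p0 − p1)]², one-sided α = 0.05.

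- For 90% power: [(1.645 × 0.4330 + 1.282 × 0.3571)/0.10]² = 136.9, so 137 patients, close to the planned 140
- For 10% power: [(1.645 × 0.4330 − 1.282 × 0.3571)/0.10]² = 6.5, so 6 to 7 patients

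The planned number fits 90% power, with 10% as the type II error.

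**Step 6: the two confidence levels.**

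*Reading A: 95% is a one-sided bound.* It uses the same 5% upper tail as the two-sided 90% interval, so the two limits are the same number. There is one test and no conflict.

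*Reading B: both are two-sided intervals.* The upper limits then correspond to one-sided 5% and 2.5% tests. For n = 140:

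| Interval | Method | Passes at | Power at 15% | Error at 25% |
|---|---|---|---|---|
| 90% | Clopper-Pearson or Wilson | ≤ 26 | 90.1% | 4.5% |
| 95% | Clopper-Pearson or Wilson | ≤ 24 | 79.9% | 1.7% |
| 90% | Wald | ≤ 27 | 93.4% | 6.9% |
| 95% | Wald | ≤ 25 | 85.6% | 2.9% |

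By Clopper-Pearson, 25 events give upper limits of 24.0% (90%) and 25.2% (95%), and 26 events give 24.8% and 26.0%. The intervals disagree at those two counts. The chance of landing there is 90.1% − 79.9% = 10.2% if the true rate is 15%, and 4.5% − 1.7% = 2.8% if it is 25%. By Wald the counts in dispute are 26 and 27.

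**The case against.** The best defence on power is that the slip is easy to see through: the same sentence calls the number sufficient, and the arithmetic shows that 10% is the type II error. That stands as far as the design goes. A reader might infer from the printed figure that the trial is underpowered or needs more patients. The article's own inputs show the reverse. But nothing else in the article corrects the figure, and condensing a protocol explains an omission, not a wrong number.

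On the confidence levels, much of the defence stands. The sentence refers to a one-sided test, which makes reading A natural, and under it nothing conflicts. The sizing sentence also ties exclusion of 25% to the 90% interval, and at n = 140 that level gives the intended power of about 90% with the Clopper-Pearson or Wilson limits. The article therefore points to a deciding level without declaring it.

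A reader might go further and infer that the plan contains two rival pass marks, so that 25 or 26 events could be declared a success or a failure once the data are seen. The article does not support that as a flat statement. It needs reading B, it needs a particular interval method (the article names none), and it needs the analysis plan, which is not shown, to be silent on the deciding level. Nor is the 6.9% error of the Wald interval a defect of this document, since the article does not choose Wald.

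What remains is narrower: the sentence mislabels confidence levels as significance levels, calls both confidence intervals, and leaves sidedness and the deciding level unstated.

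**Conclusion.** The power figure is wrong as printed. With 140 patients, a true rate of 15% and a two-sided 90% interval, power against 25% is about 90% (exact 90.1% by Clopper-Pearson or Wilson), and the stated 10% is the type II error. This conclusion does not depend on the interval method, since none of those tried comes near 10%.

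The confidence-level point holds as an ambiguity, not as a demonstrated contradiction. It has no numerical effect if 95% means a one-sided bound. If both levels are two-sided intervals, the pass mark moves by two events (26 to 24 by Clopper-Pearson or Wilson, 27 to 25 by Wald), and power under the 95% interval falls to about 80%, or about 86% by Wald. The sample size stands under the 90% interval on which it was based.

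**What to change.** Make two changes of wording in the sample-size section.

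1. Give the power as 90% (type II error 10%) in place of 10%.
2. Replace the last sentence by one rule: the primary test is one-sided at the 5% level and is judged by whether the upper limit of the two-sided 90% confidence interval, the one used for the sample size, lies below 25%. The two-sided 95% interval is reported as descriptive. Do not call 95 and 90% levels of significance.

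If the two-sided 95% interval is meant to decide, say so and restate the power as about 80%. Naming the interval method here or in the analysis plan would fix the exact pass mark.

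The cost is wording only, with no additional patients, no new data and no change in sample size. The change should be made before the primary endpoint is analysed, because it concerns the criterion for the primary test.

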## Background

Midline laparotomy is a standard method for gaining access to the abdominal cavity. However, in spite of a great number of different suture materials and techniques being available to achieve closure of the abdominal wall, the incidence of abdominal wall hernia remains high (ranging from 9% to 20%) [1-3]. The latest data show that 52% of incisional hernias occur within 6 months postoperatively, 68% within one year and 79% within two years after surgery [3,4]. They do not only require most often surgery, but even after adequate treatment, they show recurrence rates up to 45% [5]. Another complication of a complex abdominal wall closure is a burst abdomen occurring in 1% to 3% of the patients within the first days after laparotomy [6-8].

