## Methods/Design

### Study objectives

The aim of the ISSAAC-Trial is to show the safety and efficacy of MonoMax^® ^suture material. To assess its safety, parameters such as wound infections and re-operation due to burst abdomen will be evaluated. It is expected that the frequency of both parameters may be equal or lower in the ISSAAC patient cohort than in the INSECT patient cohort. To assess its efficacy, the frequency of abdominal hernias at 12 ± 1 months after surgery is taken as parameter and is also expected to may be equal or lower than in the INSECT-Trial [15,16].

The hypothesis would be that that the frequency of wound infection and of re-operation due to burst abdomen until day of discharge are equal or lower in the patient cohort enrolled in the ISSAAC-Trial compared to patients included in the INSECT-Trial.

For the ISSAAC-Trial, a standardized surgical technique of abdominal wall closure with continuous monofilament sutures is being used as it was in the INSECT-Trial. Thus, the results obtained from both trials will be comparable. To this end, only patients operated with the use of either MonoPlus^® ^or PDS^® ^as suture material during the INSECT-Trial will be included in the control group, excluding the patients randomized to interrupted sutures.

The composite primary endpoints of the ISSAAC-Trial are the frequency of wound infection, defined as redness, wound dehiscence with secretion (putrid or caliginous, smelly fluid) and/or microbiologic evidence of bacterial contamination, and the frequency of re-operation due to burst abdomen until day of discharge (see Table 1).

**Table 1 T1:** Definition of complications

Complication	Definition
Burst abdomen	Postoperatively missing continuity of the abdominal fascia in combination with a wound dehiscence and consecutive relapse operation.
Wound infection	Redness, wound dehiscence with secretion either of putrid or caliginous, smelly fluid and/or mircobiologic evidence of bacterial contamination.
Incisional hernia	A hernia is present if the ultrasound shows a fascial gap and a protruding hernial sac and the clinical exam is consistent with a hernia.
Complicated wound healing	Incision has not completely closed. Necrosis of the wound edge or primary or secondary dehiscence occurs. Formation of seroma, fistula, necrosis, and bleeding.

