Synthetic absorbable sutures which have become available over the last decade have the advantage that they are degraded by the body system and fully absorbed within 70 to 180 days. However, they lose 50% of their tensile strength already after 14 to 30 days [24]. Therefore, they may be not the optimal suture material for abdominal wall closure. The ISSAAC-Trial was designed to investigate whether the use of an ultra-long-lasting absorbable monofilament suture material is safe and prevents the occurrence of incisional hernias after primary midline laparotomy.

Several potential risk factors may have an influence on the occurrence of incisional hernias such as complicated wound healing, wound infections, obesity, chronic bronchitis or diabetes mellitus [4,25-28]. However, wound infection remains the most significant early postoperative complication in 3 to 21% of patients undergoing midline laparotomy [4,19,21,29,30]. Thus, the prevention of wound healing complications should reduce substantially the incidence of incisional hernias. Studies comparing slowly absorbable versus rapidly absorbable suture material for closing abdominal wounds showed that none of the suture materials provided satisfactory results in preventing wound healing complications. In order to evaluate the safety of MonoMax^®^, we chose as primary combined endpoint for our trial the frequency of wound infections, the frequency of complicated wound healing and the frequency of re-operation due to burst abdomen until day of discharge and defined as secondary endpoints the frequency of wound infection and healing disorders at 30 days after surgery. Since the literature shows that 50 to 70% of incisional hernias develop within one year postoperatively, we chose an additional secondary endpoint, that is the frequency of incisional hernia one year after surgery, as efficacy variable [4].

In the ISSAAC-Trial, a highly standardized surgical procedure will be used along with the suturing technique already used in the INSECT-Trial. Thus, it is reasonable to compare the results from the present trial with the data already collected during the earlier study. Because ISSAAC uses continuous monofilament suturing material, only patients enrolled in the INSECT-Trial who underwent the same treatment with MonoPlus^® ^and PDS^® ^will serve as control group.

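### The primary hypothesis is a comparison with the INSECT controls, but the only stated test and power are against a fixed 25% that the article does not link to INSECT

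*Protocol article*

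**What the plan says.** Under Study objectives, the hypothesis is that the frequencies of wound infection and of re-operation for burst abdomen up to discharge "are equal or lower in the patient cohort enrolled in the ISSAAC-Trial compared to patients included in the INSECT-Trial". The same section limits the controls to INSECT patients closed with continuous MonoPlus or PDS sutures.

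Under Statistical considerations and sample size estimation, the inference is of another kind. Interval levels are set ("The level of significance for the confidence intervals is set at 95 and 90" per cent) in order to "perform a one-sided test of significance against the 25% event rate stated in the null hypothesis". The sample size rests on the same fixed value: "Assuming a drop-out rate of 7%, 140 patients could be subjected to an analysis with respect to the primary endpoints", and this number should give a 90% interval that "would not cover the value of 25% with a power of 10% when the true event rate is at 15" per cent.

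In that section the INSECT controls serve only to set the group size. They are put first at about 80 and later at about 130.

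**The concern.** The hypothesis concerns the difference between two groups. The test concerns one proportion and a constant. The article says that 25% stands in the null hypothesis, but no hypothesis printed in it contains that figure, and nothing ties the figure to INSECT.

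The outcome of the stated test therefore does not depend on what the INSECT patients experienced. A result below 25% could be read as confirming the equal-or-lower hypothesis without having tested it. The power that justifies 140 patients likewise belongs to the fixed-value test. At stake is the main safety conclusion for a new suture material.

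**Working it through.** **Inputs from Statistical considerations and sample size estimation:** n = 140 analysed; reference rate 25%; planned true rate 15%; 90% two-sided interval (5% one-sided); controls about 80 or about 130.

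**Assumptions, because the article gives no figure:** the INSECT rate (8% to 15% shown) and a non-inferiority margin (5 and 10 points shown).

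**1. The plan's own figure.** The upper limit of the exact 90% interval is below 25% when P(X ≤ x | 140, 0.25) ≤ 0.05.

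- P(X ≤ 26 | 140, 0.25) = 0.045; P(X ≤ 27 | 140, 0.25) = 0.069.
- The limit is therefore 26 events: 26/140 = 18.6%.
- Power at 15%: P(X ≤ 26 | 140, 0.15) = 0.901.
- Normal approximation: Φ[(0.10 − 1.645·√(0.25·0.75/140)) / √(0.15·0.85/140)] = Φ[(0.10 − 0.0602)/0.0302] = 0.906.

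The printed power of 10% is not reproduced; 10% fits as the type II error (1 − 0.90). If the 95% interval decided, the limit would be 24 events and the power 0.799.

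**2. The largest passing result, set against the controls.** For 26/140, the difference is d = 0.1857 − pc, with SE = √(0.1857·0.8143/140 + pc(1 − pc)/m) and 90% interval d ± 1.645·SE.

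| Assumed INSECT rate pc | d (points) | 90% interval, m = 130 | 90% interval, m = 80 |
|---|---|---|---|
| 8% | +10.6 | +3.9 to +17.2 | +3.2 to +17.9 |
| 10% | +8.6 | +1.6 to +15.5 | +0.8 to +16.3 |
| 12% | +6.6 | −0.6 to +13.7 | −1.5 to +14.6 |
| 15% | +3.6 | −3.9 to +11.0 | −4.9 to +12.1 |

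Every row passes the fixed-25% test. At control rates of 8% and 10% the same data indicate that MonoMax is worse. At 12% and 15% the interval includes zero.

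The mismatch can also work the other way. With INSECT at 30% and MonoMax truly at 22% (both assumed), MonoMax is better, yet it passes with probability P(X ≤ 26 | 140, 0.22) = 0.19.

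**3. Power of the comparison.** For non-inferiority with 15% in both groups and a one-sided 5% level, power = Φ(margin/SE − 1.645), with SE = √(0.15·0.85·(1/m + 1/140)).

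- m = 130: SE = 0.0435. Margin 10 points: Φ(2.299 − 1.645) = 0.74. Margin 5 points: 0.31.
- m = 80: SE = 0.0500. Margin 10 points: Φ(1.998 − 1.645) = 0.64. Margin 5 points: 0.26.

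All are below the 90% of the fixed-value test.

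**The case against.** The strongest reply is that this is a condensed article. It refers to a null hypothesis that it does not print, and the origin of 25%, a margin and a comparative method may all stand in the full protocol. It clearly intends a comparison with INSECT: two surgeons are to select comparable INSECT adverse events (Safety aspects), the group size is chosen with that comparison in mind, and the Discussion defends it. The value 25% might also be an expected 15% plus a 10-point margin, which would bear on the hypothesis.

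Much of this stands. The absence of a source for 25% or of a margin is not the point here, and a reader who inferred that the controls are ignored throughout would go too far: they are unused only in the stated test and power. The article also prints no explicit success rule. What remains is that it does state a test, an error level and a power basis, and these answer a different question from the hypothesis it states.

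A reader might also infer that the false-positive rate exceeds 5%, on the ground that 25% may be an INSECT estimate treated as known. That calculation sets both groups at 25%, where the equal-or-lower hypothesis is true, so it describes a superiority claim that the article does not make. On that reading, a suture truly at 30% against controls at 25% would pass only 1.5% of the time (130 controls) or 2.9% (80), by exact calculation with the control rate re-estimated each time.

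**Conclusion.** The concern holds as a mismatch between the primary hypothesis and the only stated test, and the mismatch itself needs no assumption. Up to 26 of 140 events (18.6%) passes, irrespective of the controls. How much that matters depends on the INSECT rate, which the article does not give. At an assumed 10% the passing result is 8.6 points worse, with a 90% interval excluding zero for either control-group size; at 12% or more the interval no longer excludes zero.

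The power of about 90% belongs to the fixed-value test. For the comparison it would be about 74% or 64% with 130 or 80 controls, on the illustrative 10-point margin and 15% in both groups.

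A reader might go on to say that a suture modestly worse than control would wrongly pass. The article does not support that: without a margin, a small excess cannot be called an error, and some excesses would fall within any reasonable margin. Nor do the literature ranges in the Background and Discussion show 25% to be too high, since they are not shown to share this endpoint's definition or its window up to discharge.

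**What to change.** Reconcile Study objectives with Statistical considerations and sample size estimation, so that one primary hypothesis and one test match.

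**Preferred.** Make the primary analysis the risk difference, MonoMax minus INSECT continuous-suture controls. Use a two-sided 90% interval that includes the sampling error of the control rate (Miettinen-Nurminen, for example), judged against a margin stated and justified in advance. Keep the comparison with 25% as descriptive. Settle the control number (about 80 or about 130) and restate power for this comparison, correcting the printed 10%. An unadjusted difference does not remove case-mix differences between the two trials, so the conclusion should say so or the analysis should adjust for them.

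**Alternative.** Restate the primary aim and conclusion as a test against a 25% performance goal, justify 25%, and draw no equal-or-lower-than-INSECT conclusion from that test.

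**Cost.** Both are changes of wording and of a planned analysis on INSECT data that are already collected, and neither adds patients. The first makes the stated power less favourable; the second narrows the claim.

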### Trial organization, coordination and registration

The ISSAAC-Trial is initiated and sponsored by BBraun Aesculap and conducted by Aesculap AG in cooperation with the Coordinating Center for Clinical Trials (KKS) in Heidelberg. The KKS Heidelberg is responsible for monitoring, biometrics, database, and project management. The Sponsor's role is limited to supplying the participating trial centre with the suture material and surgical support. It is not involved in the data base management. It has taken out an insurance policy to cover all patients taking part in the trial.

The trial is coordinated by the Coordinating Center for Clinical Trials in cooperation with BBraun Aesculap. Both were responsible for management and registration (Identifier Number NCT 0005725079, ) and all trial related meetings.

The trial is performed according to the Declaration of Helsinki in its current German version, the national medical device law and the guidelines for Good Clinical Practice (GCP), as applicable.

